#### Test-weighing

For the measurement of milk intake, researchers will lend a digital electronic infant weight scale to mother for 48 h and mother will be asked to weigh her infant right before and right after a feeding, and the duration between the two weight measurements will be recorded to adjust for insensible water loss. Care will be taken to ensure that the infant is weighed with the same clothing before and after the feed. The difference in weight, adjusted for insensible water loss during the feeding period, is the amount of breastmilk the infant consumed during the feeding.

### Sample management and analysis

#### Breastmilk samples

Milk samples (foremilk) will be collected at first and final home visits. Samples will be collected separately for the analyses of milk composition and microbiota. Some milk will also be stored for measurement of milk hormones, as part of other research ongoing in our research group. The collection will be conducted by either manual expression or using a hand pump (Philips Avent, Netherlands). All samples will be stored at -80°C until analysis.

#### Stool samples

Mother and infant stool samples will be collected at first and final home visits by trained nurse and kept in a white capped opaque specimen jar. The specimen jar will be provided by the company with stabilizer in it to keep the microbiome stable. Each jar will be labelled with the baby’ name, date and time of the sample was collected. All samples will be stored at -80°C until analysis.

#### Analysis of milk composition

The macronutrient content will be measured using the Mid-infrared milk analyser (MIRIS, Sweden) at the research centre of Beijing Children’s Hospital, which will present the content of fat, protein, and total carbohydrate of the breastmilk.

#### Analysis of milk energy content

The energy content in breast milk will be estimated from the milk volume measurement using published energy values from the MOM study and the measured energy content in the sample for macronutrients analyses using the MIRIS.

#### Analysis of microbiota

The composition of microbiota in breast milk and faecal samples will be examined using the 16S rRNA based amplicon sequencing technique. The 16S rRNA based amplicon sequencing enables identification of the entire microbial community within a sample up to the species level, which can identify detailed information on the bacterial composition.

### Statistical analysis plan

All questionnaires and anthropometric data will be analysed using IBM SPSS (version 24). Intention-to-treat analysis will be performed for comparing primary outcomes (perceived stress and anxiety, infant weight and length gain from baseline to the endpoint) between intervention and control groups at the eight week postpartum using two sample t-test. Paired t-test will be used to compare baseline to post-intervention changes of each primary outcome. The association between the effects of the intervention and the frequency of use will be examined by two-tailed Pearson correlation. Two-sample t-test will be used to compare the changes in milk volume, energy and macronutrients level between intervention and control group. Regression analysis will be used to adjust for confounding factors.

Furthermore, associations between infant temperament/behaviour and the composition of microbiota in mother’s breastmilk, mother and infants’ gut will be examined using univariate ANOVA. Multiple regression analysis and MANOVA will be used to detect differences among significant predictor variables identified by ANOVA.

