### Hypotheses and outcome measures

#### Primary hypotheses

The use of a relaxation therapy by breastfeeding mothers of LPI and ETI that will be given from one week to eight week postpartum, will result in:
reduced maternal stress and anxietygreater infant growth, specifically increased weight and length gain

Primary outcomes and measures
maternal stress and anxiety at one week and eight week postpartum, measured by Chinese version of Cohen’s Perceived Stress Scale (PSS) and Beck Anxiety Inventory (BAI) respectively.infant weight and length gain (as SD scores) from 1- to 8-week measured using anthropometry.

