### Sample size

The number of mother-infant pairs required was calculated using the conventional formula [24] for two sample t-test:
*N* = 16*(SD^2^/D^2^) (N = number per group, SD = standard deviation, D = Difference between group).

The SD and D were obtained from the results of the MOM study [10], which assessed the effects of relaxation meditation tape on reducing maternal stress assessed by PSS between intervention and control groups (D = 3.13, SD = 5.00). A sample of 82 mother-infant pairs (41 per randomised group) would allow the detection of a 3.13 points difference in perceived stress between groups at 80% power with a significance level of 0.05. Considering the microbiome analysis in the present study will only be conducted in vaginal delivered mothers, which account for approximately 40% of the total sample, a larger sample is required. However, the effect size in the present study may be larger than the MOM study, as mothers with preterm infants are likely to be more stressed than mothers with healthy term infants, which were examined in the MOM study. Thus, a total of 120 infants will be recruited.

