## Discussion

One of the strengths of our study is that it has been designed to minimize disruption for the participants since the data collection points have been timed to coincide where possible with routine clinic visits and home visits. According to the health policy in China, the maternity leave is 98 days. During this time, the majority of mothers will practice a traditional postpartum confinement at home and keep routine contact with the community clinic where they are registered. In Beijing, most community clinics will schedule a routine home visit at one week postpartum for all registered mothers. Hence, the baseline assessment of this study is scheduled at one week postpartum when the trained clinic nurses conduct their routine home visit. Thus our baseline assessment and data collection can be conducted during their routine home visit to reduce imposing an extra interruption and additional burden on the mother. Moreover, since there is a routine contact, the nurse can provide the scale and the eight week questionnaires during the contact one week prior to the eight week data collection. Mothers can fill in the questionnaires using their leisure times and return the scale and questionnaires when they take their infant to the clinic for the second month vaccination; the nurse can also conduct the eight week sample collection and infant anthropometry measurement during the time when mothers bring their infants to the clinic for vaccination. These routine contacts with local clinics should help to reduce the potential attrition rate.

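### Four primary outcomes each get their own t-test with no rule for combining them; if any one can carry a primary claim, the false-positive chance is about 14–18.5%

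*Protocol article*

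**What the plan says.** Under Primary hypotheses, the protocol article sets out two domains with two measures each. The maternal domain is "maternal stress and anxiety at one week and eight week postpartum", measured by PSS and BAI respectively. The infant domain is "infant weight and length gain (as SD scores) from 1- to 8-week measured using anthropometry".

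The Statistical analysis plan section treats all four as primary. It provides for an intention-to-treat analysis "comparing primary outcomes (perceived stress and anxiety, infant weight and length gain from baseline to the endpoint". Each of these comparisons is made "between intervention and control groups at the eight week postpartum using two sample t-test". It also adds within-group paired t-tests for each primary outcome. The section gives no significance level, no hierarchy and no success criterion.

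The only alpha in the article is in Sample size, where a 3.13-point PSS difference is to be detected "at 80% power with a significance level of 0.05". That section gives "A sample of 82 mother-infant pairs (41 per randomised group" and then raises the target: "Thus, a total of 120 infants will be recruited". BAI, weight gain and length gain have no sample-size basis.

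**The concern.** With four primary outcomes in two domains, the plan has to say what counts as a positive trial. It could require all four, both outcomes in a domain, any one, or PSS first and the others after it. These rules have different error rates and different power, and the article picks none of them.

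The gap leaves the choice open until results are known. Stress, anxiety, weight or length could each come out below 0.05 by chance, and that one result could be presented as confirming the primary hypothesis. The article says that it aims to show causal relationships, so the strength of its primary claim matters. The sample size also depends on the rule, because the number needed for PSS changes with the alpha at which PSS is tested.

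**Working it through.** **Inputs from the article.** D = 3.13 PSS points, SD = 5.00, alpha 0.05, power 80%, 41 per group, 120 in total (Sample size). Four primary outcomes, each with a two-sample t-test (Statistical analysis plan).

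**Assumptions.** The 120 are split 1:1, as the 41-per-group calculation implies. The article gives no correlations among outcomes, so these are varied. It gives no attrition rate, only that routine clinic contacts "should help to reduce the potential attrition rate", so 20% loss is used for illustration: 60 × 0.8 = 48 per arm.

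**Step 1: reproduce the plan's figure.** 16 × SD²/D² = 16 × 25/9.797 = 40.83, rounded up to 41 per group, 82 in total. This agrees with the article. The constant 16 approximates 2 × (1.96 + 0.84)² = 15.7, so the test is two-sided. The t-test power at 41 per group is 79.96%. The sample size is right for PSS alone.

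**Step 2: chance of at least one false positive if any one result suffices.** All four null hypotheses are taken as true, with each test at two-sided 0.05.

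- Independent tests: 1 − 0.95⁴ = 0.1855.
- Correlation r between the two tests within a domain, none between domains: 1 − q(r)², where q(r) is the probability that both statistics in a domain stay within ±1.96.

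| Within-domain r (assumed) | 1 − q(r), one domain | 1 − q(r)², all four |
|---|---|---|
| 0 | 9.75% | 18.5% |
| 0.5 | 9.1% | 17.3% |
| 0.7 | 8.3% | 16.0% |
| 0.9 | 7.0% | 13.6% |

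Correlation between domains lowers the figure a little further. By simulation it is 17.0% with 0.5 within and 0.2 between, and 15.6% with 0.5 throughout. The paired t-tests are not counted here.

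**Step 3: the same tests under a conjunctive rule.** If both outcomes in a domain must be significant, the false-positive rate for that domain under the same null is 0.05 + 0.05 − (1 − q(r)). For r = 0 this is 0.10 − 0.0975 = 0.25%; for r = 0.7 it is about 1.7%. There is no inflation, but a lower chance of success.

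**Step 4: what control costs for PSS.** Holm compares the smallest of the four p-values with 0.05/4 = 0.0125. Standardised effect: 3.13/5.00 = 0.626. Two-sample t-test power:

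| Evaluable per arm | alpha 0.05 | alpha 0.0125 | alpha 0.0125, baseline-adjusted (r = 0.5 assumed) |
|---|---|---|---|
| 41 | 80.0% | 61.1% | 76% |
| 48 | 85.9% | 69.8% | 83.8% |
| 60 | 92.5% | 81.2% | 92.1% |

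The adjusted column uses 0.626/√(1 − 0.5²) = 0.723. At 0.0125 unadjusted, 80% power needs 59 per arm (58.5 rounded up), or 118 evaluable pairs. The planned 120 covers that only with almost no loss.

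**The case against.** The strongest reply is that a multiplicity rule often sits in a fuller analysis plan, and that a condensed article which omits one has not thereby declined to adjust. The section is two paragraphs long and nowhere says that no adjustment will be made. This stands as far as intent goes. It does not clear the article, which fixes four primary outcomes, the test for each and a sample size based on one of them. Followed as written, that leaves the primary conclusion undefined.

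A reader might infer that the trial promises a 5% error rate for its primary family and breaks the promise. The article does not say so: 0.05 is the design level for PSS, and its use for the other three outcomes is inferred because no other level appears.

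A reader might also infer that the plan adopts an any-one-suffices rule. It does not. The hypotheses are worded conjunctively (stress and anxiety; weight and length), and under a both-in-domain rule the inflation disappears, as Step 3 shows. If the two domains are separate claims and either outcome suffices in each, the rate is about 7–10% per domain.

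Finally, listing one-week PSS and BAI under primary outcomes might suggest that a baseline score will be tested as an outcome. Study design and Randomisation and blinding make that visit the baseline assessment, and the Statistical analysis plan compares groups at eight weeks. The point is editorial.

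**Conclusion.** The concern holds in conditional form. The article names four primary outcomes with separate tests and does not say how they combine into a conclusion. If any one can support a primary claim, the chance of at least one false-positive primary result is about 14–18.5%, roughly three to four times 0.05. That range rests on the any-one rule, on 0.05 for each test, and on assumed correlations. Even 0.9 within both domains leaves 13.6%.

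The stated 82 pairs are correct for PSS at 0.05. It would be wrong to call control nearly free: at 60 per arm PSS power drops by about 11 percentage points (92.5% to 81.2%), and at 48 per arm by about 16 (85.9% to 69.8%). The adjusted figures of 92% and 84% need an assumed baseline correlation of 0.5 and a baseline-adjusted primary analysis, whereas the article specifies t-tests and mentions regression only for confounding factors. Whether the other three outcomes have adequate power cannot be judged from the article.

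**What to change.** Before unblinded analysis, state the decision rule and control family-wise error at two-sided 0.05 across the four eight-week between-group comparisons. Holm is a suitable default. Two alternatives also resolve the point: name PSS, the only powered outcome, as the single primary outcome and make the other three secondary; or fix a testing order that starts with PSS. Either keeps PSS at 0.05. The first gives up the primary status of the other outcomes, and the second stops confirmatory testing at the first non-significant result.

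If Holm is chosen, restate the power in Sample size: for 3.13 PSS points at 0.0125, 81% with 60 evaluable per arm and 70% with 48 per arm, with the 20% loss labelled as an assumption. If baseline adjustment is made the primary analysis, give 92% and 84% as conditional on a baseline correlation of 0.5. Say plainly that no power has been calculated for BAI, weight gain or length gain.

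As a minor edit, describe the one-week PSS and BAI under Primary hypotheses as baseline values.

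All of this is wording and needs no new data. The real cost is the per-test power given up under Holm, which leaves unadjusted PSS power below 80% once evaluable numbers fall under 59 per arm.

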### Randomisation and blinding

The baseline assessment will be conducted during the one week postpartum home visit. After recording the demographic characteristics of mothers and their early feeding experience, participants will be randomly assigned to either intervention arm or control conditions (standard management) by randomisation envelope. A member of the research team who will have no contact with participants will produce the randomisation schedule using a computer random number generator, and prepare the assignments in sealed opaque envelopes. Randomisation will be stratified by gestational age (34–35 weeks, 36–37 weeks), delivery mode (vaginal, caesarean), and by the study centre (four community clinics). Participants will not know about the randomisation until the end of the study; they will be aware that the aim of the study is to investigate factors that may make breastfeeding easier for mothers with an LPI or ETI, so they can breast-feed for longer. The researchers will be blinded during the data analysis process; however, they cannot be blinded during data collection since additional materials (diary for recording the use of relaxation tape) will be collected during the data collection period.

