### Data collection

Measures of maternal stress, anxiety, infant behaviour and appetite will be recorded at each home visit; participants can choose to fill the questionnaires on paper or online in their own time after the visit. A breast milk sample will be collected pre-feed and infant anthropometry will be assessed by a trained nurse pre-feed at each home visit. Feed duration will be noted by the trained nurse. Details about the data collection in each visit are shown in Fig. 3.

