### Questionnaires

Questionnaires that will be used in this study are outlined in Table 2. All questionnaires are available in Chinese. The Chinese version of PSS, BAI, BEBQ, and IIFAS have been used among postnatal women in previous studies, which have presented reasonable validity and reliability.

**Table 2 Tab2:** Questionnaires for the BABY study

Questionnaire	Time point for the use of questionnaires			
	First visit 1 week	Final visit 8 week	3 month follow-up	6 month follow-up
Demographic questionnaire	✓			
Perceived stress scale	✓	✓		
Beck Anxiety Inventory	✓	✓		
Baby Eating Behaviour Questionnaire	✓	✓	✓	✓
Iowa Infant Feeding Attitudes Scale	✓	✓	✓	✓
3 day Infant Behaviour Diary	✓	✓		

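### The named primary test is an unadjusted two-sample t-test that uses no stratification factor and uses baseline at most by subtraction; this costs precision but does not inflate type I error

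*Protocol article*

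**What the plan says.** All places are in the protocol article.

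- **Statistical analysis plan, primary test.** The primary outcomes are compared by intention to treat "between intervention and control groups at the eight week postpartum using two sample t-test". Growth is listed there as "infant weight and length gain from baseline to the endpoint"; the outcome list under Primary hypotheses expresses it in SD scores.
- **Statistical analysis plan, second test.** "Paired t-test will be used to compare baseline to post-intervention changes of each primary outcome". The text does not say whether this is done within each arm.
- **Statistical analysis plan, adjustment.** "Regression analysis will be used to adjust for confounding factors". No covariate, outcome or rank relative to the t-test is given.
- **Primary hypotheses and Table 2.** The psychological outcome is "maternal stress and anxiety at one week and eight week postpartum", so week-1 PSS and BAI exist. Weight and length are also measured at both visits (Anthropological measurements).
- **Randomisation and blinding.** Allocation takes place at the one-week visit and is stratified by two gestational-age bands and by "delivery mode (vaginal, caesarean), and by the study centre (four community clinics"). Blocking is not mentioned.
- **Data collection.** For the questionnaires, "participants can choose to fill the questionnaires on paper or online in their own time after the visit".

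**The concern.** Stratifying the allocation and measuring the outcome at baseline both pay off only if the analysis uses them. A plain t-test on week-8 values leaves the part of the variance predictable from baseline in the error term, and lets a chance imbalance in week-1 stress pass into the estimate. A t-test on gains uses baseline, but with a fixed coefficient of 1, which is less efficient than estimating it. If allocation is balanced within strata, variation between strata that the design has already removed from the arm comparison is still counted as error.

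The paired t-tests raise a separate problem. Stress may fall after the first week without any tape, and infants gain weight and length anyway. A significant change from baseline is therefore not evidence about the intervention, yet it is easily read that way.

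The regression sentence does not resolve this. It fixes neither the covariates nor the rank of the adjusted result. If applied to the primary outcomes, it would leave two answers to the same question.

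**Working it through.** **Inputs from the protocol article.** PSS difference D = 3.13, SD = 5.00, alpha 0.05, power 80%, 41 per group required, 120 recruited (Sample size); 2 × 2 × 4 = 16 strata, on average 120/16 = 7.5 pairs each (Randomisation and blinding).

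**Assumed, not in the documents.** Baseline-to-week-8 correlation r; share of outcome variance explained by strata; block size; natural PSS fall; SD of change. Power figures assume no dropout.

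**1. The plan's own figure.** 16 × 5.00² / 3.13² = 40.8, so 41 per group. Power at 41 per group by noncentral t is 80.0%. The figure reproduces. At 60 per arm the same unadjusted test has 92.5%.

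**2. PSS compared as week-8 values.** Adjusting for baseline multiplies residual variance by 1 − r²; the effective sample size is 120/(1 − r²).

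| r | 1 − r² | 120 mothers act like | Power, 60 per arm |
|---|---|---|---|
| no adjustment | 1 | 120 | 92.5% |
| 0.3 | 0.91 | 132 | 94.6% |
| 0.5 | 0.75 | 160 | 97.5% |
| 0.6 | 0.64 | 188 | 98.9% |

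**3. PSS compared as changes.** Relative variance is 2(1 − r). At r = 0.3 this is 1.4, and power at 60 per arm falls to 82.6% (normal approximation, on which the week-8 comparison has 92.9%). At r = 0.5 the two are equal. Whether week-8 values or changes are compared therefore matters.

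**4. Growth.** The variance of ANCOVA relative to the gain score is (1 − r²)/[2(1 − r)] = (1 + r)/2. At r = 0.5 this is 0.75 (25% lower); at r = 0.7 it is 0.85 (15% lower).

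**5. Ignoring the strata.** Simulated trials had N = 120, 16 strata, additive stratum effects and no treatment effect. The table gives the two-sided error of the plain t-test at nominal 5%, as the range over repeated simulations of 6,000 to 8,000 trials each.

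| Variance explained by strata | Blocks of 4 within strata | No blocking |
|---|---|---|
| 10% | 3.8–4.5% | 4.8–4.9% |
| 20% | 2.7–3.4% | 4.9–5.2% |
| 30% | 2.1–2.5% | 4.7–5.0% |

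The t-test is conservative only if allocation is blocked within strata; otherwise it holds its level. In one of the blocked simulations its mean 95% interval width for PSS was about 3.61 points. Adjusting for strata gave 3.43, 3.24 and 3.03 points at 10, 20 and 30%.

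**6. Paired t-test when the tape does nothing.** 60 mothers, SD of change 5, noncentrality = fall/(5/√60).

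| Natural PSS fall (points) | 0.5 | 1 | 1.5 | 2 |
|---|---|---|---|---|
| Noncentrality | 0.77 | 1.55 | 2.32 | 3.10 |
| Chance of p < 0.05 | 12% | 33% | 63% | 86% |

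**The case against.** The strongest defence is that nothing here threatens validity. A two-sample t-test after randomisation is unbiased, its error rate is at or below nominal, and on the protocol's own PSS inputs it has 92.5% power at 60 per arm. Regression adjustment is announced, and an article may leave its details to a fuller plan. All of that stands. It limits the point to efficiency and prespecification, but does not remove it. The article does name the primary test, and that test omits the stratification factors. The sample size also rests on PSS alone, although BAI, weight gain and length gain are primary too. For an assumed standardised effect of 0.4, power at 60 per arm is about 58% on raw final values and 71% with ANCOVA at r = 0.5.

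A reader might infer more than the documents support:

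- *That the primary analysis ignores baseline altogether.* Growth is a gain in SD scores, which uses the one-week value. For PSS and BAI the sentence can be read as week-8 values or as changes.
- *That the t-test's error rate is wrong for this design.* This needs blocking, which is not stated, and the departure is then conservative.
- *That the trial is underpowered for stress.* On the stated inputs it is not.
- *That the paired tests are the plan's test of efficacy.* The between-group comparison is stated first, and the paired tests are not said to be run per arm or used to judge the tape.
- *That the regression for confounders should go entirely.* The same section correlates effect with frequency of tape use. Use is self-selected, so confounding is a real issue there.

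A fair objection also applies to the remedy. Allocation is at the one-week visit (the Abstract places it before that visit), and questionnaires may be completed afterwards. Some week-1 PSS and BAI scores could therefore follow allocation and already reflect the tape, and adjusting for them could bias the estimate. Weight and length, measured at the visit itself, are less exposed.

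**Conclusion.** The point holds as a loss of precision and a gap in prespecification, and merits a change before analysis. The named primary test uses no stratification factor and uses baseline by subtraction at most. For r between 0.3 and 0.6, adjusting a week-8 comparison removes 9 to 36% of residual variance. The power gain for PSS is modest, because the unadjusted test already exceeds 90%. For growth the variance saving over the gain score is 15 to 25% for r between 0.7 and 0.5. The stratification adds a further gain only if strata predict the outcome: under blocking, the t-test's true error would fall from about 4.5% to between 2 and 2.5% as strata explain 10 to 30% of variance. The paired tests carry no information about the tape; how misleading they could be depends on the natural drift in stress, which the documents do not give. Every size quoted beyond the plan's own 41 per group and the 92.5% rests on assumed values.

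**What to change.** 1. For each primary outcome, prespecify one ANCOVA as the primary analysis: the eight-week value (SD score for weight and length) on arm, the one-week value of the same measure, gestational-age stratum, delivery mode and clinic. Enter the stratification factors as main effects, since 16 cells average only 7.5 pairs. Report the adjusted difference with its 95% confidence interval.
2. Keep the unadjusted two-sample t-test as a sensitivity analysis, and say whether it compares week-8 values or changes.
3. Require week-1 PSS and BAI to be completed before the envelope is opened, and record the time of completion. Where a mother's baseline was completed after allocation, do not use it as a covariate; adjust for strata only. Reconcile the Abstract with the Randomisation section on when allocation occurs.
4. Report within-arm changes as means and SDs, without p-values.
5. State that the regression for confounders does not apply to the randomised primary comparison, and keep it for non-randomised analyses such as frequency of tape use.

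Cost: 1 + 1 + 3 + 1 = 6 degrees of freedom out of 120 pairs, revised wording, and a small change to questionnaire timing at the first visit. No new variable is needed apart from the completion time, and SPSS fits the model.

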### Intervention tool: the relaxation therapy recording

The tape used in this study is based on a meditation CD designed for breastfeeding mother [25]. The recording was transcribed and translated into Chinese language by a certified yoga therapist. A brief version of the recording was tested and compared with other four relaxation techniques in a pilot study [26] and was demonstrated to be the most effective approach for breastfeeding mothers to relax. Mothers in the intervention group will be given the tape and will be asked to listen to the recording as frequently as possible while breastfeeding or expressing milk, preferably at least once a day. Mothers will be asked to record their use of the tape in a diary book.

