In the MOM study [10], the milk intake was measured by the stable isotope method (deuterium dilution). However, the local investigators thought that this would discourage Chinese mothers from participating. Hence, we elected to use the conventional 48-h test-weighing method for the measurement of milk intake, by calculating the difference between the infant’s weight immediately before and after each breastfeeding during a 48-h period. Data will be adjusted for any extra water consumed, water derived from oxidation of milk macronutrients, and water stored in fat and protein (calculated from body water and weight change and published values for protein and water contents of lean body mass) during analysis. A previous study compared the accuracy of test-weighing and the stable isotope method, and showed no significant difference between the two methods by paired t-test [35]. However, both methods might have potential sources of error. The calculation of water output depends on the assumption that the mean loss of water subject to fractionation applies to all infants. A mean value based on recent data in Chinese infants will be used to reduce the bias. Moreover, based on previous research, a 100% error in this figure will only result in 1% error in water output [35].

To control for the influence of antibiotics on maternal gut and milk microflora, the assessment of microbiota will be conducted in mothers who were vaginally delivered their infants, since the delivery mode has been shown to influence infant’s gut microbiota. We will also record the antibiotic use of all mothers and infants at the baseline and follow-up assessments. While the microbiota can be influenced by maternal diet, this would be expected to be balanced between treatment group and control group.

In summary, this study aims to show causal relationships between maternal psychological state and breastfeeding outcomes, which may mediate infant behaviour and the gut microbiota. To our knowledge, the present study will be the first RCT that investigates the role of HMO and microbiota in mother-infant signalling. Findings of this study may identify modifiable factors which can be used to encourage and support exclusive breastfeeding.

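### The planned correlation of intervention effects with frequency of use is an unadjusted, within-arm association with self-chosen use; adjust it for baseline and label it exploratory

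*Protocol article*

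**What the plan says.** The Statistical analysis plan section of the protocol article fixes the method in one sentence: "The association between the effects of the intervention and the frequency of use will be examined by two-tailed Pearson correlation". It does not say which variable represents those effects. The per-mother quantities it offers come from neighbouring sentences: the outcome at eight weeks, and the change from baseline ("Paired t-test will be used to compare baseline to post-intervention changes of each primary outcome").

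The section headed Intervention tool sets out how use arises. Mothers in the intervention group "will be asked to listen to the recording as frequently as possible while breastfeeding or expressing milk, preferably at least once a day". Measurement is by self-report: "Mothers will be asked to record their use of the tape in a diary book". Controls receive standard management and have no recording.

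Two other sentences in the Statistical analysis plan matter. The randomised comparison is separate: "Intention-to-treat analysis will be performed for comparing primary outcomes", by two-sample t-test. The paragraph also ends with a general statement: "Regression analysis will be used to adjust for confounding factors". That sentence names no covariates and is not attached to the frequency-of-use analysis.

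**The concern.** The wording treats a within-arm association as if it measured what the recording does. An individual effect is the difference between a mother's outcome with the recording and her outcome without it, and only one of these is ever seen. Her own change, or her own eight-week value, combines any effect with natural course, regression to the mean and prognosis.

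Use is also chosen after allocation. Mothers who start out more stressed may listen more and then fall back towards the average. Mothers with more help or a more settled infant may listen more and do better anyway. Because listening is tied to feeding and expressing, mothers who feed more often have more occasions to listen, and feeding frequency may itself go with infant weight gain, which is a primary outcome. Randomisation protects against none of this, because only one arm enters the correlation.

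At stake is the interpretation of a supporting result. A significant coefficient could be read as showing that more listening does more good, and a null one as showing that the amount does not matter. Neither reading would be safe.

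**Working it through.** **The plan's own figure.** The article gives no figure for this correlation. Its only related calculation is the sample size, "at 80% power with a significance level of 0.05": 16 × 5.00² / 3.13² = 400 / 9.797 = 40.83, so 41 per group and 82 in total. This reproduces the stated number, and nothing below alters it.

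**Inputs.**
- Number with use data: 120 / 2 = 60. This assumes equal allocation (the Sample size section describes equal groups), no attrition and complete diaries.
- Effect of the recording: zero, by construction.
- Correlation ρ between baseline and eight-week PSS: assumed 0.3, 0.5 or 0.7.
- Correlation *a* between use and baseline PSS: assumed 0.3 or 0.5.

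The documents give none of these correlations, so the results are an illustration over a range and not an estimate for this trial.

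**Formula.** Standardise both scores. With no effect, and use related to the eight-week score only through baseline, the covariance of use with change is −a(1 − ρ) and the variance of change is 2(1 − ρ). Hence

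corr(use, change) = −a √((1 − ρ)/2).

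A negative value means that heavier users appear to improve more.

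**Chance of a significant Pearson test.** By Fisher's z this is Φ(|z| − 1.96) plus a negligible opposite tail, with z = atanh(r) × √57. For example, with ρ = 0.3 and a = 0.3, r = −0.3 × √0.35 = −0.177, |z| = 0.179 × 7.55 = 1.35, and the probability is about 27%.

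Simulation of 20,000 trials per setting agrees and adds the baseline-adjusted test:

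| ρ | a | mean r with change | significant, unadjusted | significant, adjusted for baseline |
|---|---|---|---|---|
| 0.3 | 0.3 | −0.175 | 26.9% | 5.0% |
| 0.3 | 0.5 | −0.295 | 64.6% | 4.9% |
| 0.5 | 0.3 | −0.149 | 21.4% | 5.3% |
| 0.5 | 0.5 | −0.249 | 49.5% | 5.1% |
| 0.7 | 0.3 | −0.116 | 14.7% | 5.0% |
| 0.7 | 0.5 | −0.192 | 31.8% | 5.2% |

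With use unrelated to prognosis, the unadjusted rate is the nominal 5%.

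**Direction.** The bias can run either way. If less stressed mothers listen more (a = −0.3), mean r becomes +0.12 to +0.18, which could hide a real association. The undefined outcome variable matters too. If the eight-week value is used in place of change, the same mechanism gives corr = a × ρ, from 0.3 × 0.3 = +0.09 to 0.5 × 0.7 = +0.35, so heavier users appear worse off. One source of confounding therefore gives opposite signs depending on a choice the article leaves open.

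**What baseline adjustment cannot remove.** Suppose instead that use correlates 0.3 with a better course that baseline does not predict. The correlation with change is then significant in 46% to 58% of trials unadjusted, and in 64% to 65% after baseline adjustment. That part can be handled only by how the result is described.

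**The case against.** The strongest reply is that this is one sentence about a supporting analysis in a condensed article. The sentence says only that an association will be examined. It does not mention dose-response or causation, and it does not name the outcome variable. The closing regression sentence may be meant to cover it, with covariates left to a fuller plan. Any description of use must lie within the intervention arm, because controls have nothing to use. The percentages rest on assumed correlations: under those assumptions the association is real, so a significant result is not an error of the Pearson test but a matter of interpretation.

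Most of this stands, and it limits the point. A reader might infer that the authors plan to claim a dose-response, especially since the Discussion says that "this study aims to show causal relationships between maternal psychological state and breastfeeding outcomes". The documents do not support that inference: the stated aim concerns psychological state and breastfeeding outcomes, not how often the recording is played. A reader might also infer that the correlation should give way to an instrumental-variable analysis. That goes too far. With randomised arm as the only instrument and zero use in controls, such an estimate is essentially the intention-to-treat effect divided by mean use. It does not show whether heavier users benefit more.

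The reply leaves the stated method untouched. A Pearson correlation takes no covariates, the general regression sentence is not tied to it, and the phrase used for its outcome describes something that cannot be observed for an individual mother.

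**Conclusion.** The point holds as a minor one. The article specifies an unadjusted correlation, within one arm, between self-chosen use and an undefined quantity that it calls the effects of the intervention. With no effect at all and 60 mothers, a correlation of 0.3 to 0.5 between use and baseline stress would make the correlation with change significant in about 15% to 65% of trials. Baseline adjustment returns this to about 5%. These figures depend wholly on assumed correlations, on change being the variable used, and on full diary data from equal arms. They show what could happen and do not predict what will. The sign can reverse, and confounding by unmeasured factors would survive adjustment. The randomised comparison of primary outcomes and the sample size are not affected.

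**What to change.** Replace the Pearson correlation with a regression, within the intervention arm, of each eight-week outcome on diary-recorded frequency of use. Adjust for the baseline value of that outcome and for the stratification factors (gestational age, delivery mode, centre). Name the outcome variable. Describe the result as an exploratory, non-randomised association between use and outcome, drop the reference to effects of the intervention, and draw no causal dose-response conclusion from it.

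The cost is a few lines of analysis and a sentence of text; the diary, baseline scores and stratification factors are already collected.

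An instrumental-variable analysis with randomised arm as the instrument is an optional addition. It should state its assumptions: allocation acts only through listening, and the effect per session is linear. Because it rescales the intention-to-treat effect, it does not replace the within-arm analysis.
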